## Abstract

**Methods::**

Fifty-two children between 7 and 12 years of age with a diagnosis of mouth breathing and halitosis determined through an interview and clinical examination will be selected. The participants will be divided into 4 groups: Group 1—treatment with brushing, dental floss and tongue scraper; Group 2—brushing, dental floss and aPDT applied to the dorsum and middle third of the tongue; Group 3—brushing, dental floss and probiotics; Group 4—brushing, dental floss, aPDT and probiotics. The use of a breath meter and microbiological analysis of the tongue coating will be performed before, immediately after treatment and 7 days after treatment. The quantitative analysis will involve counts of colony-forming bacteria per milliliter and real-time polymerase chain reaction. The normality of the data will be determined using the Shapiro–Wilk test. Parametric data will be submitted to analysis of variance and nonparametric data will be compared using the Kruskal–Wallis test. The results of each treatment in the different periods of the study will be compared using the Wilcoxon test.

**Discussion::**

Due to the low level of evidence, studies are needed to determine whether treatment with aPDT using annatto as the photosensitizer and blue led as the light source is effective at diminishing halitosis in mouth-breathing children.

## 1. Introduction

Halitosis is a term that defines any odor that emanates from the oral cavity, the origin of which may be local or systemic.^[1]^ The odor may be attributed to a variety of products resulting from the metabolism of bacterial amino acids. Halitosis is classified as genuine, pseudo-halitosis and halitophobia. Genuine halitosis is divided into physiological halitosis (caused mainly by coated tongue) and pathological halitosis, which can be oral (oral disease) or extraoral (systemic diseases). Pseudo-halitosis is self-perceived by the individual even when not perceived by others and not diagnosed clinically. Halitophobia is a condition in which the patient complains of bad breath even with no clinical or social evidence and after specific treatments.^[2]^

The prevalence of halitosis is high, with the literature reporting rates of more than 50%.^[3]^ This condition is considered an important social factor that interferes with interpersonal relationships. Besides causing concerns related to physical health, halitosis can be a social barrier and lead to psychological problems.^[4]^ In this context of social and biological importance, the prevalence of halitosis and associated factors in the pediatric population has been investigated throughout the world and different rates are estimated.^[1,5–10]^

Recent studies involving mouth-breathing children have demonstrated that this group has a significantly greater frequency of halitosis compared to nose breathers.^[8,11–13]^ Halitosis classified as oral originates in the mouth and upper airways and results from the decomposition of organic matter—epithelial cells are retained in the posterior portion of the tongue due to low salivary flow and/or a water imbalance as well as microbial attack in the oral environment, which favor the growth of proteolytic bacteria, resulting in the production of volatile sulfur compounds, which are related to the characteristic odor.^[14,15]^ When salivary flow rate is low, the bacterial count and halitosis in the oral cavity increase. The change from nose breathing to mouth breathing causes changes in the dental arches and surrounding tissues, such as anatomic changes in the palate and the drying of the surface of the mucosa, which is one of the main complaints of mouth breathers and may be related to halitosis.^[3,16]^ Individuals who breath through the mouth due to adenotonsillar hypertrophy have higher rates of halitosis compared to treatment groups submitted to surgery and control groups (nose breathers).^[10]^

Volatile sulfur compounds (VSCs) are related to the occurrence of halitosis. Hydrogen sulfide is associated with coated tongue, methyl mercaptan is associated with periodontal pockets and dimethyl sulfide is associated with systemic alterations.^[5,17–19]^ Among the different methods for the diagnosis of halitosis, the clinical examination, known as the organoleptic test, is a subjective method consisting of smelling the odor exhaled from the mouth and nose and quantifying this odor with the use of a scale. VSCs can be measured with the use of sulfide monitors and gas chromatography.^[2,5,11,20]^ The portable Breath-Alert device (BA) has been used with increasing frequency in clinical practice for the diagnosis of halitosis due to its ease of use and low cost.^[16,21–25]^ In children, who need fast, practical exams, the BA is a halitosis detection tool with high sensitivity and specificity for use in pediatric dentistry.^[8]^

Conventional treatments used in the control of halitosis consist basically of the use of toothpastes and mouthwashes containing bactericidal substances, a tongue scraper, the treatment of dental caries and periodontal disease and the control of xerostomia.^[26]^ Some studies suggest that amine fluoride has a positive effect on diminishing halitosis.^[3]^ Alternative treatments, such as antimicrobial photodynamic therapy (aPDT)^[10,21,27]^ and probiotics, have also been employed in an attempt to control this condition.^[3,16,22,23,26]^ Antimicrobial PDT is treatment in which a photosensitizing agent (dye) produces oxygen free radicals in the presence of light, leading to bacterial cell death. As the main etiological factor of halitosis is the presence of anaerobic bacteria, aPDT (red laser and methylene blue) has demonstrated positive results on the reduction of hydrogen sulfide as well as the bacterial load on the dorsum of the tongue.^[15,21]^ The dye annatto has been evaluated as a photosensitizer in studies on halitosis. This extract from the seeds of the plant Bixa orellana, which is native to Brazil, is accepted by the World Health Organization due to the fact that it is nontoxic.^[1]^ Annatto has antioxidant and antimicrobial properties^[9]^ and recent studies have demonstrated its potential as a therapeutic agent and natural dye.^[28]^

Probiotics are microorganisms that provide health benefits when absorbed by the host and are often used in foods and fermented products as well as pharmaceutical formulations.^[25]^ Studies have shown the positive results of probiotics for the control of halitosis and suggest that these products favor the elimination of undesirable microorganisms and promote the recolonization of the microbiota.^[16,22]^

Alternatives such as aPDT with annatto and the administration of probiotics for the reduction in or elimination of halitosis in pediatric dentistry are less invasive methods that involve natural components, which reduces harm to oral tissues and avoids the occurrence of bacterial resistance. The major challenge is the development of an effective, lasting treatment protocol for halitosis in children that eliminates the anaerobic bacteria related to this condition and reestablishes the microbiota of the dorsum of the tongue, thereby improving quality of life. The use of probiotics in dentistry constitutes innovative treatment capable of modifying the oral microbiota as an alternative to the use of antibiotics and other antimicrobial agents.

The treatment of halitosis is a topic that requires greater attention, and the results of this study can assist in clinical decision making with regards to the use of probiotics and aPDT with blue light-emitting diodes (LEDs) for the treatment of this condition, as most dentists have this light source in their offices and the portable sulfide meter is inexpensive to acquire. Moreover, the use of annatto as a photosensitizer is an innovative approach. As the light source and photosensitizer are accessible, this treatment is expected to be easily and effectively reproducible clinical practice. Probiotics and aPDT are expected to be effective at diminishing halitosis in mouth-breathing children.

The main of the study is to determine whether treatment with aPDT using annatto as the photosensitizer and blue led as the light source is effective at diminishing halitosis in mouth-breathing children.

## 2. Methods

### 2.1. Study registration

This is the first version of a protocol that was registered in ClinicalTrials.gov, under the registration number: NCT05590897, first posted on 10/21/2022 and last updated on 10/21/2022. Available online at: https://clinicaltrials.gov/ct2/show/NCT05590897.

### 2.2. Type of study

A randomized, controlled clinical trial was designed based on the Consolidated Standards of Reporting Trials statement. It is described according to the criteria established in the Standard Protocol Items: Recommendations for Interventional Trials statement and Figure 1 is the Standard Protocol Items: Recommendations for Interventional Trials figure.

**Figure 1. F1:**
[figure not shown]
SPIRIT figure as recommended by 2013 SPIRIT statement.

### 2.3. Ethics committee

The study will be conducted in accordance with the ethical precepts stipulated in the Declaration of Helsinki (World Medical Association Declaration of Helsinki, 2008). The protocol for this study was approved by the Human Research Ethics Committee of Universidade Metropolitana de Santos-UNIMES (certificate number: 64510922.6.0000.5509). All information will be contained in the statement of informed consent in accordance with Resolution 196 of the National Board of Health (Health Ministry, Federal District, Brazil, March 10, 1996). The guardians of the children will agree to participate by signing a statement of informed consent; 2 copies of which will be signed—one for the guardian and one for the researchers.

The participants will be informed that they may withdraw from the study at any time for any reason, if they so wish. The researchers will also be able to remove participants from the study if deemed necessary.

### 2.4. Participants

The study will include Male and female children 7 to 12 years of age who enter the dental clinic of Universidade Metropolitana de Santos (UNIMES), for treatment. At the first appointment, a form addressing the medical history of the patient will be completed. The volunteers will then be submitted to a clinical examination for the determination of oral health status. Next, the inclusion and exclusion criteria will be applied.

#### 2.4.1. Inclusion criteria.

Children and adolescents with a diagnosis of mouth breathing determined using a standard questionnaire and halitosis determined using a portable breath meter (score ≥ 2) will be included in the study.

Parents/guardians will provide data on family income, parent’s schooling, child’s previous experience with dental treatment, the occurrence of snoring, open mouth during sleep, daytime sleepiness, saliva on the pillow during sleep, awaking with thirst during the night, dry mouth, nocturnal enuresis, headache, aggressivity, inattention, hyperactivity, abnormal respiration, swallowing difficulty, sense of smell and taste, speaking, negative effect on school performance and the presence of allergies. Parents/guardians will also report their child’s toothbrushing frequency, their participation in brushing, the child’s eating habits, child’s toothpaste, the occurrence of poor oral habits, such as bruxism, nail biting, lip biting, tongue bite, tongue pushing, smacking the lips and whether they have detected bad breath in their child or themselves.

#### 2.4.2. Exclusion criteria.

Nose breathers, individuals with dentofacial anomalies (e.g., hare lip and cleft palate), those in orthodontic and/or orthopedic treatment, those in oncological treatment, those with systemic (gastrointestinal, renal or hepatic) conditions, pregnant girls, individuals having undergone antibiotic treatment in the previous month and individuals with fissured tongue will be excluded.

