### 2.7. Randomization

The type of treatment will be determined randomly for each patient prior to the intervention. Randomization will be generated electronically using the randomizer.org site for the balanced distribution of the children among the groups.

Fifty-two mouth-breathing children with a diagnosis of halitosis will be selected and divided into 4 groups.

Group 1: Treatment with brushing, dental floss and tongue scraper;

Group 2: Brushing, dental floss and aPDT applied to the dorsum and middle third of the tongue;

Group 3: Brushing, dental floss and probiotics;

Group 4: Brushing, dental floss, aPDT and probiotics.

Breath meter results will be determined before, immediately after treatment and 7 days after treatment. Microbiological analysis of the tongue coating will performed at the same times. The quantitative analysis will be performed using direct plating and real-time polymerase chain reaction (PCR).

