**Figure 3. F3:**
[figure not shown]
Breath odor analysis with breath meter.

To avoid the influence on the breath analysis results, the participants will be instructed to obey the following: in the 48 hours prior to the evaluation, avoid foods with garlic, onion, strong spices, the consumption of alcohol and the use of an oral antiseptic; on the day of the evaluation, abstain from all food in the 2 hours prior to the exam, abstain from coffee, mints, chewing gum, oral and personal hygiene products with perfume (aftershave, deodorant, perfume, creams and tonic) and brush only with water.

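### The entry washout covers antibiotics but not probiotics, so existing probiotic users can join any group and the probiotic contrasts may be attenuated

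*Protocol article*

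**What the plan says.** Section 2.4.2 sets one time-limited rule on prior exposure, the antibiotic rule: "individuals having undergone antibiotic treatment in the previous month and individuals with fissured tongue will be excluded". Probiotics do not appear in the list.

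The instructions to participants in section 2.8.2 (text under Figure 3) ask them, for 48 hours before an evaluation, to "avoid foods with garlic, onion, strong spices, the consumption of alcohol and the use of an oral antiseptic". On the day itself they add limits on food, coffee, mints, chewing gum and perfumed products. Probiotic products are not named.

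Entry requires "halitosis determined using a portable breath meter (score ≥ 2) will be included in the study" (section 2.4.1). Guardians also report, among other items, "the child’s eating habits, child’s toothpaste, the occurrence of poor oral habits", and section 2.4 has a medical history form. Neither source is tied to a criterion on probiotics.

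Two arms in section 2.7 receive the study probiotic: "Group 3: Brushing, dental floss and probiotics" and "Group 4: Brushing, dental floss, aPDT and probiotics". The Introduction describes probiotics as "often used in foods and fermented products as well as pharmaceutical formulations" and states: "The use of probiotics in dentistry constitutes innovative treatment capable of modifying the oral microbiota". The Discussion says that the trial will also determine whether halitosis falls after probiotic treatment.

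**The concern.** The protocol screens out one recent exposure that acts on oral bacteria but not another that it describes as widespread and active on the same bacteria, and that is itself a randomised treatment. Followed as written, the criteria admit a child on a daily probiotic supplement, and nothing in the article asks that child to stop.

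At stake is the trial's second question, the probiotic effect. Existing users in Groups 1 and 2 may already have part of the effect. Existing users in Groups 3 and 4 have less to gain from the study product. Both push the probiotic contrasts toward no difference. If prior use is neither excluded nor known, a null probiotic result would be hard to tell apart from background use.

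**Working it through.** **Inputs.** Section 2.6 gives two-sided α = 0.05, power 0.90, 13 children per group and 52 in total. It defines the effect size but gives no means, variances or numerical value, so n = 13 cannot be reproduced forward. It can only be solved backward. The share c of children already using a probiotic, and the strength k of their product relative to the study product, are not in the documents. Both are assumptions here.

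**Step 1: effect implied by the stated design** (normal approximation, one pairwise contrast).

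d = (1.960 + 1.282) × √(2/13) = 3.242 × 0.392 = 1.27 standard deviations. On the article's own scale, which divides by the root of the summed variances, this is 1.27/√2 = 0.90. A two-sample t calculation gives d = 1.33.

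**Step 2: how background use changes the contrast.** Take Group 4 v 2, which as listed differ only by the probiotic. Let δ be the full probiotic effect, and suppose that the study product adds nothing beyond δ in a child already using another product.

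- Follow-up level: the mean probiotic benefit is ckδ in Group 2 and δ in Group 4. The difference is (1 − ck)δ.
- Change from baseline: stable users in Group 2 gain nothing new. In Group 4, non-users gain δ and users gain (1 − k)δ. The mean is (1 − c)δ + c(1 − k)δ = (1 − ck)δ.

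The shrinkage is the same on either scale. With k = 1 the factor is 1 − c.

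**Step 3: power with 13 per group.** Power = Φ(3.242 × (1 − ck) − 1.960).

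| Share c | Expected users per 13 | Power, k = 1 | Power, k = 0.5 | n per group to restore 0.90 (k = 1) |
|---|---|---|---|---|
| 0% | 0 | 0.90 | 0.90 | 13 |
| 5% | 0.65 | Φ(1.120) = 0.87 | 0.89 | 15 |
| 10% | 1.3 | Φ(0.958) = 0.83 | 0.87 | 17 |
| 20% | 2.6 | Φ(0.634) = 0.74 | 0.83 | 21 |

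The last column is 13/(1 − c)², rounded up; for example 13/0.81 = 16.05, so 17. With k = 1, t-based power agrees to within 0.001.

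**Step 4: which contrasts are touched.** Group 4 v 2 is the clean probiotic contrast. Group 3 v 1 differs in addition by the tongue scraper, which section 2.7 lists for Group 1 only (section 2.8.6 speaks of scraping all participants). The aPDT contrast with equal probiotic allocation, Group 4 v 3, and the contrast between the two arms without the study probiotic, Group 2 v 1, are not directly affected, because prior users are expected equally on both sides.

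**The case against.** A reader might infer that the probiotic contrasts are in fact diluted. The documents do not support that. They give neither the share of users nor any basis for treating ordinary products as equivalent to the study product, which is a named strain with xylitol taken three times a day. Entry at a breath score of 2 or more also selects users whose product has not resolved their halitosis, which limits k. At 5% use, or with weak products, the loss is small. All of this stands.

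The 0.90 power comes from data on photodynamic therapy, not on probiotics, and the planned comparisons are analysis of variance with Tukey's test or Kruskal–Wallis, not a single z-test. This also stands: the table shows how fast power falls under stated assumptions, and does not estimate this trial's power.

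A reader might also infer bias in favour of one arm. Randomisation spreads prior users over all four groups, so the expected effect is attenuation, although chance imbalance is possible with 13 per group.

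It can be argued that stable use is present at baseline too and so cancels in before–after comparisons. This does not hold for the between-group contrast: users in Group 4 have less to gain, and Step 2 gives the same shrinkage on change scores.

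Finally, a journal article may leave detail to the full protocol. That is a fair answer on how antibiotic or probiotic use between readings is recorded, and no criticism is made there. It is a weaker answer on eligibility, which the article sets out item by item, down to fissured tongue and the antibiotic window.

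**Conclusion.** The gap is real: as written, current probiotic users with a qualifying breath score are eligible for every group and are not asked to avoid their own product. The consequence is conditional. If use is not rare and the products act like the study product, the probiotic contrasts may be attenuated toward no difference by a factor 1 − ck. Under full equivalence, power for one contrast would move from 0.90 to about 0.87, 0.83 or 0.74 at 5%, 10% or 20% use. With half-strength products it would be 0.89, 0.87 or 0.83. These figures rest on assumed c and k, on no added benefit of the study product in children already at full effect, and on the stated 0.90 taken at face value.

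The point bears on the probiotic question and not directly on aPDT, the stated main objective. It is worth correcting because the change to the criteria is small.

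**What to change.** - Extend the antibiotic criterion in section 2.4.2 to recent use of probiotic supplements or preparations. The investigators should choose and justify the window; the existing one-month antibiotic window is one option.
- Ask all four groups to avoid non-study probiotic supplements until the 7-day reading, and analyse every child in the allocated group whether or not this was followed.
- Limit the rule to supplements and preparations. The article itself says that probiotics are common in foods, so barring all such foods could remove many children.

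The cost is one phrase in the criteria, one question on the medical history form already planned, and one added instruction to participants. Some children would be excluded or re-screened later, so recruiting 52 may take longer. Some attenuation from probiotic foods would remain possible.

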### 2.5. Patient and public involvement

The guardians of the patients were not involved in the design of this study. After the data analysis, the guardians will be given the opportunity to participate in a result-sharing meeting if they so desire. The consent form signed by guardians of the participants explains that the storage of data for each participant and family member is within the terms of confidentiality.

### 2.6. Calculation of sample size

The sample size will be calculated using data from the study by Costa da Mota et al.^[21]^ An error $err=\left|\underline{x_{1}}-\underline{x_{2}}\right|$ was first established, in which $\underline{x_{1}}$ and $\underline{x_{2}}$ are the means of the groups at baseline for periodontal treatment with PDT. The effect size was calculated based on this error as follows:

$$\begin{array}{l} \frac{err}{\sqrt{\sigma_{1}^{2}+\sigma_{2}^{2}}} \end{array}$$

in which $\sigma_{1}^{2}$ and $\sigma_{2}^{2}$ are the variances of Groups 1 and 2, respectively.

Assuming that the groups studied have normal or approximately normal distribution, that the sample size will be sufficiently large and that a 2-tailed test will be used for a significance level of α = 0.05 and maintaining a test power of 1 − β = 0.90, n = 13 will be needed for each group. Figure 2 shows that a sample of 52 children (4 groups of 13 individuals) would enable demonstrating statistically significant differences while maintaining a test power equal to or higher than 0.90. If the hypothesis of normality of the distributions is rejected, the sample size should be corrected by approximately 5%.

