### 2.9. Statistical analysis

Data from the portable Breath-Alert™ device will be analyzed for normality using the Shapiro–Wilk test. Parametric data will be submitted to analysis of variance followed by Tukey’s test when necessary and the *t* test will be used for paired data to analyze the results of treatment in the 2 periods of the study. Nonparametric data will be compared using the Kruskal–Wallis test followed by the Student–Newman–Keuls test when necessary and the Wilcoxon text will be used for the comparison of each treatment in the 2 periods of the study.

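### The power of at least 0.90 with 13 children per group rests on a difference between two group means at baseline, and is not shown to apply to the planned four-arm comparisons.

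*Protocol article*

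**What the plan says.** Section 2.6 takes its data from an earlier study. It defines an error as the absolute difference between two means, which "are the means of the groups at baseline for periodontal treatment with PDT", and divides this by the square root of the summed variances of Groups 1 and 2. It assumes normal or nearly normal data and a sufficiently large sample, and states that "a 2-tailed test will be used for a significance level of α = 0.05". With power 0.90 it finds that "n = 13 will be needed for each group". It then says that 52 children in four groups of 13 "would enable demonstrating statistically significant differences while maintaining a test power equal to or higher than 0.90", with reference to Figure 2. The section adds: "If the hypothesis of normality of the distributions is rejected, the sample size should be corrected by approximately 5" percent.

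Section 2.9 plans the analysis of the Breath-Alert score. "Parametric data will be submitted to analysis of variance", followed by Tukey's test when necessary; nonparametric data go to Kruskal–Wallis followed by Student–Newman–Keuls. Section 3 says that the study will establish whether the proposed treatments differ. The score runs from 0 to 5 (section 2.8.2), and entry requires 2 or more (section 2.4.1).

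**The concern.** Three features of section 2.6 do not fit the trial it is meant to size.

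- **The effect.** A difference between group means at baseline says nothing about response to treatment. In a randomised comparison its expected value is zero. The text gives no time point after treatment, no numeric difference and no SD.
- **The comparison.** Two means and two variances describe one comparison of two groups. The trial has four arms, an omnibus test and pairwise follow-up. Multiplying 13 by four does not carry the 0.90 over to those tests, and 13 per arm is hardly a large sample.
- **The non-normality correction.** It depends on rejecting normality, which section 2.9 tests on the trial's own data, while the total is fixed at 52. At entry the score can take only four values (2, 3, 4 or 5), so non-normality is likely.

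The 0.90 figure is the only justification given for 52 children. If it does not belong to the planned tests, readers cannot tell which differences the trial can reliably detect.

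**Working it through.** **Inputs from section 2.6:** two-sided α = 0.05, power 0.90, n = 13 per group, 52 in total, effect size ES = err/√(σ₁² + σ₂²). The values of err and the variances are not given, so the 13 cannot be reproduced. It can only be solved backwards.

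**Assumption:** n came from the usual two-group normal formula that matches this ES, n = (z₀.₉₇₅ + z₀.₉₀)²/ES². Section 2.6 does not print this formula.

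**Implied effect.**
- (1.960 + 1.2816)² = 10.507.
- n exactly 13: ES = √(10.507/13) = 0.899.
- n just above 12, rounded up to 13: ES = √(10.507/12) = 0.936.
- With equal variances σ₁² = σ₂² = σ², the difference in SD units is d = √2 × ES = 1.27 to 1.32.

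**Power at 13 per group for that d, normal data.**

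| Test | d = 1.27 | d = 1.32 |
|---|---|---|
| One two-sample t test (noncentral t, 24 df, noncentrality d√(13/2)) | 0.875 | 0.899 |
| Tukey pair among four groups (studentized range, 48 df) | 0.717 | 0.758 |
| ANOVA, 3 and 48 df: two arms differ by d, two lie midway (noncentrality 13d²/2) | 0.746 | 0.783 |
| ANOVA: one arm differs from three equal arms (13d² × 3/4) | 0.907 | 0.930 |
| ANOVA: two arms against two (13d²) | 0.971 | 0.980 |

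Under this assumption a Tukey pair would need about 18 to 20 per group for power 0.90.

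**Detectable difference at 13 per arm, 90% power, normal data.** Solving the same functions for d gives 1.33 SD for one prespecified two-group contrast and 1.56 SD for a Tukey pair.

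**Alternative readings of the 0.90.**
- If Figure 2 is an omnibus ANOVA curve, 0.90 at N = 52 requires f = 0.544. Tukey pairwise power is then 0.55 when the arms split two against two (d = 2f = 1.09), and 0.89 when one arm is high, one low and two midway (d = f√8 = 1.54).
- If the printed ratio was entered as Cohen's d in a two-sample t calculation, it would be about 1.33. The true standardised difference would be 1.33 × √2, about 1.88, and power would exceed 0.90.

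**Non-normality correction.** 13 × 1.05 = 13.65, which rounds up to 14 per group, or 56 in total. The plan keeps 52.

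**The case against.** The best defence is that nothing printed is shown to be miscalculated. Section 2.6 gives an effect-size ratio and no sample-size formula. Figure 2 plots power against total sample size, which could be a four-group calculation. The omnibus ANOVA meets 0.90 at the back-solved difference under two of the three patterns of means. The text promises significant differences, not 0.90 for every pair. The words about baseline may be loose phrasing for change from baseline or for data from the cited study. All of this stands, and it rules out two stronger readings that a reader might infer: that the 0.90 definitely comes from the two-group formula, and that the trial's power is below 0.90. The documents support neither.

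Non-normal data would go to Kruskal–Wallis with Student–Newman–Keuls, not Tukey, so a Tukey power reduced by a further 5% would match no planned analysis. Student–Newman–Keuls is stepwise and never less powerful than Tukey. Simulated on normal data at the same differences, its power for the pair is about 0.73 to 0.78 with the other arms midway, and 0.81 to 0.86 for the one-against-three and two-against-two patterns. This only approximates the rank version. The loss is smaller but remains.

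Keeping 52 does not contradict a correction that is conditional. The difficulty is only that its condition is resolved after the size is fixed.

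None of these points repairs the stated input. Even if Figure 2 is a four-group curve, the effect described in the text is a baseline difference between two groups.

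**Conclusion.** The point holds in limited form: the claim of power of at least 0.90 is wrongly founded as written, and is not shown to apply to the four-arm comparisons in section 2.9. Whether the true power is above or below 0.90 cannot be settled from the article.

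The size of the discrepancy rests on the assumed two-group formula, equal variances and normal data. On those terms a single t test roughly meets the claim, a Tukey pair falls short by about 0.14 to 0.18 (0.90 − 0.76 and 0.90 − 0.72), and the omnibus test may fall on either side. The baseline input and the missing four-group basis do not depend on those assumptions; they can be read directly from section 2.6.

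**What to change.** Keep 52 children and rewrite section 2.6.

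1. Replace the baseline error with a between-arm difference in Breath-Alert score after treatment, or in change from baseline. Give its numeric value, SD and time point. If the baseline wording was a slip, correct it.
2. State which test and which contrast the power refers to, and what Figure 2 plots.
3. Restate the claim as a detectable difference. On a normal scale, 13 per arm gives 90% power for about 1.33 SD in one prespecified contrast and about 1.56 SD for a Tukey pair.
4. Since non-normality is likely, say now that the rank-based route has somewhat less power at 52, by the plan's own 5% allowance, rather than leaving a size correction to depend on a test of the trial data.

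The cost is one rewritten section and a less favourable power statement. No extra children are needed.
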